### Session procedure

Participants will be invited to the Donders institute for brain cognition and behavior on two session days separated by approximately 6 months. Each session will include the following procedures: (1) hair and blood sampling. (2) practice of fMRI tasks, including the calibration of MVC for the two fMRI tasks. The practice session is done in a dummy scanner to ensure same body position during handgrip-calibration, practice and fMRI-scanning. (3) MRI scanning, including six scans and a 15 minute break: structural MRI, fMRI during task1, MRS, break, fMRI during task2, DTI and resting state. (4) Behavioral and neuropsychological testing. The order is kept the same across subjects and sessions. An overview of a session day is given in Fig. 2. Written informed consent is given on the first session day. Trait measures such as the adult reading test are only assessed on the first test day. POMS measurements are assessed before sampling, during the break and after behavioral testing. The total duration of each session will be about 5 hours. For CFS patients, questionnaires are assessed as part of the clinical routine of the ECCF prior to the session days. For healthy controls, questionnaires are assessed at home through an internet link, sent to the subjects by email.

**Fig. 2 Fig2:**
[figure not shown]
Flowchart of fMRI session day. MVC = Maximal voluntaty contraction, MRI = Magnetic resonance imaging, fMRI = functional MRI

### Analysis

The aim of this project is to explore the neural mechanisms of change underlying (successful) CBT for CFS. Accordingly, we will include all patients that completed both sessions for analysis of CBT effects. Statistical analysis will be done to 1) compare outcome measures between CFS patients and healthy controls at baseline, 2) compare changes between baseline and second assessment between patients that had CBT and waiting list and 3) compare changes between baseline and second assessment between CFS patients within the CBT condition that show clinical significant improvement (see above) and those that do not. Following previous reports [13, 14], relationship between neural outcome measures and clinical outcome measures, physical activity levels and neuropsychological functioning will be assessed. Multiple mediation analyses will be conducted to explore whether neural outcome measures mediate therapy effects on clinical outcome measures (Preacher and Hayes, [91]).

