## Methods/design

### Study design

A RCT will be conducted to investigate neural correlates of change brought on by CBT in patients diagnosed with CFS. CFS patients will be randomly assigned to either the intervention group (N = 60), which will immediately start with CBT, or the waiting group (N = 30), which will start with CBT after a 6 months waiting period. In order to compare CFS patients that recover from CBT with those that do not we will use a 2:1 allocation ratio for CBT and waiting group respectively. MRI measurements, behavioral measures, questionnaires and biomarker sampling will be gathered at baseline and at a second session after approximately 6 months in both groups. Results will be compared to 30 age, gender and education matched healthy controls, which will also be tested twice, separated by a 6 months period (Fig. 1).

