### Study population and recruitment procedure

A total of 90 female CFS patients and 30 age and education matched female healthy controls will be recruited from the ECCF of the radboudUMC in Nijmegen, the Netherlands. Only female patients are included for homogeneity. Patients that are referred to the ECCF of the Radboudumc, are diagnosed with CFS according to the US Centers for Disease Control and prevention (CDC) consensus-criteria ([66]; Reeves et al., [2]), and scoring 40 or higher on the subscale fatigue severity of the Checklist Individual Strength (CIS) and have a total score of 700 or higher on the Sickness Impact Profile 8 (SIP8) will be informed about the study by their treating psychologist during their first intake session at the ECCF. If the patients agree, they will receive an information folder. The investigator will call the patients after a one week reflection period to answer any further questions and to ask for participation. If willing to participate, and meeting all in- and exclusion criteria (Table 1), patients will be invited for the first testing day at the Donders institute for brain cognition and behavior. Age and education matched female healthy controls will be recruited though advertisements and through flyers in the patients folder. Interested healthy controls will receive an information folder and the recruitment procedure will follow the same steps as described above. Written informed consent will be given at the first session day. Randomization of patients will take place after the first session day. The Mini-international Neuropsychiatric Interview (M.I.N.I) will be used to rule out any current psychiatric disorders.

**Table 1 Tab1:** Inclusion and exclusion criteria

Inclusion criteria	
1.	Female
2.	Age between 18 and 55 years
Additional inclusion criteria for CFS patients	
1.	CFS diagnosis according to the CDC-criteria ([66]; Reeves et al., [2]);
2.	Fatigue severity subscale (CIS) score ≥40
3.	Severely disabled, defined by scoring ≥ 700 on the Sickness Impact Profile (SIP)
4.	Eligible for treatment with CBT
Additional inclusion criteria for healthy controls	
5.	Fatigue severity subscale (CIS) score ≤ 35
Exclusion criteria	
1.	Current use of psychotropic medication (e.g. antidepressants)
2.	Contra-indication for MR-examinations (e.g. claustrophobia)
3.	Abnormal hearing or (uncorrected) vision

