### Sample size

Power calculation is based on current standards in neuroimaging. For (f)MRI, the recommended number of subjects for between-group designs is 20 (Thirion et al., [92]). In addition, from previous studies we know that groups of 20 subjects per condition are sufficient to detect significant differences in (neuro) physiological parameters measured with fMRI [17, 18]. Similarly, a group of 22 subjects were sufficient to detect significant treatment effects measured with MRI [13]. Based on previous work at the ECCF (Knoop et al., [5]) it is assumed that approximately 50 % of the CFS patients in the CBT condition will show significant improvement (for definition: see above). Accordingly, to be able to compare successfully treated patients with non-successfully treated patients we will include twice as many patients in the CBT condition as in the waiting list condition. Assuming that 10 % of the measurements (from baseline as well as 2nd assessment) will yield technically insufficient data, 17 % of the patients will drop out from the study and a ratio of 2:1 (CBT: waiting list), we will include 30 healthy controls, 30 patients in the waiting list condition and 60 patients in the CBT condition (Fig. 3). Based on previous clinical work (Knoop et al., [74]; Wiborg et al., [9]), we expect a mean decline of–15.2 (±15.8) for patients in the CBT condition and–5.2 (±7.2) for patients in the waiting list condition. Accordingly, assuming an alfa of 0.05 and a power of 0.95 this will also yield enough power to replicate previous reported treatment effects on the primary clinical outcome measures. Note that technical failure of MRI measurements will not affect the collection of clinical measures.

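### The randomised CBT versus waiting-list comparison is described as a comparison of changes with no baseline adjustment; adding the pre-randomisation baseline as covariate for scalar outcomes is a nearly free gain in precision

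*Protocol article*

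**What the plan says.** The Analysis section lists three comparisons. The second is the only randomised one: "compare changes between baseline and second assessment between patients that had CBT and waiting list". No model, test or covariate is named. For this comparison "we will include all patients that completed both sessions for analysis of CBT effects".

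Under Study design, the measures "will be gathered at baseline and at a second session after approximately 6 months in both groups". Under Study population and recruitment procedure, "Randomization of patients will take place after the first session day"; the Randomization section agrees. Session-1 measures are therefore taken before allocation is known. One exception is possible: the section on cytokines and cortisol lets the home saliva samples be taken up to two weeks before or after the test day.

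The Sample size section plans the clinical outcome on the change scale: "we expect a mean decline of–15.2 (±15.8) for patients in the CBT condition and–5.2 (±7.2) for patients in the waiting list condition", and "assuming an alfa of 0.05 and a power of 0.95 this will also yield enough power". It plans "30 patients in the waiting list condition and 60 patients in the CBT condition" and assumes that "17 % of the patients will drop out from the study". It also assumes that 10% of measurements are technically unusable at each assessment, and notes that this does not affect clinical measures.

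**The concern.** A change score fixes the coefficient on baseline at 1. In a randomised comparison, a model with baseline as covariate estimates the same treatment effect but takes the coefficient from the data. Where the session-to-session correlation is modest, the best coefficient is well below 1. The change score then over-corrects any chance difference between arms at baseline, and the excess appears as noise in the estimated effect.

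Chance differences are not negligible here. With 40 and 20 patients, the standard error of the standardised baseline difference is sqrt(1/40 + 1/20) = 0.27 SD, so a difference above 0.25 SD in either direction arises in about 36% of trials. At an assumed r of 0.5, an imbalance of 0.27 SD shifts the difference in change by (1 − 0.5) × 0.27 = 0.14 SD. Over repeated randomisations this is lost precision, not bias. At stake is power for the imaging, behavioural and biomarker contrasts, for which the documents show no margin.

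**Working it through.** **1. The plan's own figure.** Inputs from Sample size: difference 15.2 − 5.2 = 10.0; change SDs 15.8 and 7.2 (± read as SD, scale read as CIS fatigue); alpha 0.05, taken as two-sided; power 0.95; ratio 2:1.

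- Averaged SD = sqrt((15.8² + 7.2²)/2) = 12.28.
- Waiting-list n = (1.96 + 1.645)² × 12.28² × (1 + 1/2) / 10² = 29.4, so 30, with 60 in CBT. Power at 60/30 is 0.954. The figure reproduces.
- After 17% dropout (about 50 and 25), the variance with separate SDs is 15.8²/50 + 7.2²/25 = 7.066 and power is 0.964. With the averaged SD it is 0.914.

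**2. Patients available.** Clinical: 30 × 0.83 ≈ 25 and 60 × 0.83 ≈ 50. Paired imaging, with a 10% failure at each session: 30 × 0.83 × 0.9 × 0.9 ≈ 20 and 60 × 0.83 × 0.81 ≈ 40.

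**3. Equal SDs (s) at both sessions.** Var(change) = 2s²(1 − r). Var(residual given baseline) = s²(1 − r²). Ratio = (1 + r)/2.

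| r (assumed) | Variance ratio | Reduction in SE | Equivalent extra patients, 2/(1+r) − 1 |
|---|---|---|---|
| 0.3 | 0.65 | 19% | 54% |
| 0.5 | 0.75 | 13% | 33% |
| 0.7 | 0.85 | 8% | 18% |
| 0.9 | 0.95 | 2.5% | 5% |

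Illustration at 40/20, with an assumed r of 0.5 and a true effect of 0.6 SD (normal approximation): the change SD is 1.0 SD, so power = Φ(0.6/0.274 − 1.96) = 0.59. After adjustment the SD is sqrt(0.75) = 0.866, so power = Φ(0.6/0.237 − 1.96) = 0.72.

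**4. CIS fatigue, where SDs are not equal.** Entry at 40 or more on a scale ending at 56 confines baseline to 40–56; an SD of 4.6 (uniform) is assumed. The follow-up SD implied by a change SD c is r × 4.6 + sqrt(c² − 4.6²(1 − r²)), and an arm's slope is r × follow-up SD / 4.6.

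At r = 0.4 the follow-up SDs are 17.07 and 7.68, and the slopes are 1.48 and 0.67. A common-slope fit uses about (50 × 1.48 + 25 × 0.67)/75 = 1.21. The residual variances are then 246.2 and 55.8, and the variance is 246.2/50 + 55.8/25 = 7.156. Ratio to change: 7.156/7.066 = 1.013, a slight loss.

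Over r = 0, 0.2, 0.3, 0.4 and 0.6 the ratios are 0.82, 0.94, 0.99, 1.01 and 0.97, with power between 0.962 and 0.986 against 0.964. At a baseline SD of 6 and r = 0.6 the ratio is 1.017. At the limiting SD of 8, which needs every patient at 40 or 56, it is 1.035 for r = 0.6.

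**5. What the interaction term does.** With arm-specific slopes and centred baseline, the large-sample variance is the sum of residual variances over n, plus (difference in slopes)² × SD0²/N. At r = 0.4: 17.07² × 0.84/50 + 7.68² × 0.84/25 + (1.484 − 0.668)² × 4.6²/75 ≈ 7.06, a ratio of about 1.00. The loss disappears, but no gain replaces it.

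**6. Why robust standard errors.** An ordinary fit pools the variance: (49 × 15.8² + 24 × 7.2²)/73 = 184.6. The variance of the difference becomes 184.6 × (1/50 + 1/25) = 11.08 instead of 7.066, and power falls to 0.852 instead of 0.964. For CIS, pooling would cost more than adjustment gains.

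**The case against.** The strongest case against is that this is a preference about efficiency in a condensed article, on a matter often left to the analysis plan. Much of it stands.

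- A reader might infer that the plan commits to raw, unadjusted change scores. The text does not say so. Regressing change on arm and baseline gives the same arm coefficient and standard error as regressing the session-2 value on them, so a baseline-adjusted analysis is compatible with comparing changes. An analysis plan that is not shown may already contain it.
- A reader might infer that adjustment is never less precise. With a common slope, 2:1 allocation and unequal SDs, that fails slightly for CIS (step 4).
- A reader might infer that about 20 waiting-list patients limit every contrast. That number applies to paired imaging only; clinical outcomes keep about 25, and nothing ties scan failure to blood, hair or behavioural data.
- No SD or correlation is given for metabolites, task activation, reaction times, cue bias, cytokines or cortisol, so the size of their gain is unknown.
- Adjusting scalar outcomes while keeping change maps for voxel-wise results would leave two models for one contrast.

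None of this removes the point. Change is the only scale the article names, baseline adjustment appears nowhere, and a pre-randomisation baseline exists for nearly every outcome.

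**Conclusion.** The point holds as a low-severity improvement. The plan contains no error here and no stated figure is wrong.

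Where SDs are similar at both sessions, adjustment reduces variance by 35% at r = 0.3 and 5% at r = 0.9. This rests on correlations that the documents do not supply. Grey matter volume, if highly repeatable, would gain little. For CIS fatigue the result runs from a clear gain when r is near 0 to none, or a loss of about 1–2% with a common slope, under assumed baseline SDs of 4.6 to 6; the clinical comparison does not depend on it. The practical value lies in outcomes of modest repeatability, above all the imaging scalars with about 20 and 40 patients. The documents do not support a conclusion that the trial is underpowered because of change scores.

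**What to change.** Add to the second comparison in the Analysis section: for scalar outcomes (regional volumes, metabolites, regional task contrasts, behavioural measures, biomarkers, CIS fatigue, SIP8), the CBT versus waiting-list effect is estimated by regressing the session-2 value, or the change, on arm with the same measure's baseline as covariate. Include a centred baseline-by-arm term, to avoid the small loss from unequal slopes, and use robust standard errors, to allow for unequal variances. If only one is adopted, robust standard errors matter more for CIS.

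Three limits belong with it:

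- Use the baseline only where it was collected before randomisation. Saliva taken after the first test day needs a date check.
- Do not carry it to improved versus not improved, or to patients versus healthy controls. Those groups are not randomised and may differ systematically at baseline.
- Voxel-wise change maps may stay; say in the text that the scalar results use the adjusted model.

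The cost is one or two sentences and at most two extra parameters per model. No new data are needed and no patient with a valid change score is lost. If the analysis plan already adjusts for baseline, the sentence merely brings the article into line.

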So far, definitive evidence for this argument is limited because the few existing studies have often used small samples sizes and lacked a patient control group. The inclusion of a patient control condition is necessary to attribute changes seen in the treatment group to the intervention, rather than to time per se or to changes occurring irrespective of the treatment. In this study we will address these issues and aim to further investigate neural mechanisms underlying CFS and its change by CBT using anatomical and functional magnetic resonance imaging (MRI) in a large-sample randomized controlled trial (RCT). In this RCT, we will compare changes between CFS patients that had CBT (N = 60) with patients that were allocated to a waiting period (N = 30). By including the large treatment group we will also be able to investigate the relationship between neural changes and treatment response. Patients will be compared with healthy controls (N = 30) who are also tested twice, separated by 6 months, to control for test-retest effects.

This study will investigate neural mechanisms underlying CFS symptoms and its changes after CBT. The aims are threefold. First, we aim to replicate previous found anatomical CBT-related changes in grey matter volumes [14] using anatomical MRI and qualify these findings by exploring changes in metabolite concentrations and white matter integrity using magnetic resonance spectroscopy (MRS) and diffusion tensor imaging (DTI). Second, we aim to explore the mechanisms of change of CBT for CFS using functional MRI (fMRI) and behavioral testing. Finally, we aim to investigate immune and endocrine functioning in CFS and its change after CBT by assessing various biomarkers in blood, saliva and hair. These three aims are discussed in more detail below.

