### Outcome measures

#### Primary clinical outcome measures

Fatigue severity will be measured using the subscale fatigue severity of the CIS consisting of 8 items scored on a 7-point Likert Scale with a total score ranging between 8–56 (Vercoulen et al., [71]). Higher scores indicate higher levels of fatigue. This questionnaire has been validated extensively in patients with CFS ([72, 73]; Vercoulen et al., [71]; Vercoulen et al., [42]). Following previous reports (Prins et al., [69]; Wiborg et al., [10]) we will use cut-off score of ≥ 40 for inclusion of severely fatigued CFS patients.

Successful treatment is defined by a clinically significant improvement on the CIS sub-scale fatigue severity, i.e. scoring lower than 35 and a reliable change index of >1.96 on the CIS subscale fatigue (Knoop et al., [74]). The cut-off score of 35 has frequently been used as a criterion to indicate clinically relevant fatigue in clinical studies (Knoop et al., [5]; Wiborg et al., [75]).

Functional impairment will be measured in CFS patients using the Sickness Impact Profile 8 [76]. The SIP8 contains 85 statements about health-related dysfunction in 8 areas domains (home management, ambulation, mobility, intellect, social interactions, sleep/rest behaviour, recreation and work). In completing the SIP, the patient is asked to check only those statements that she is sure describe her on a given day and are related to her health. The eight subscales are added to provide one weighted score of disability (SIP8 total, range 0–5799) (Knoop et al., [5]; Prins et al., [69]; Wiborg et al., [9]). Higher scores indicate higher levels of experienced disabilities. Functional impairment will be defined as a SIP score higher than 700.

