## Discussion

This study will investigate neural mechanisms underlying CFS symptoms and its changes after CBT. The aims are threefold. First, we will replicate and extend previously found anatomical findings, second, we will explore underlying neural mechanisms using functional neuroimaging and third, we will collect biomarker measures from blood, hair and saliva to assess cytokine and cortisol changes during CBT.

To our knowledge, this will be the first randomised controlled trial investigating neural mechanisms of change brought on by CBT for CFS. There are a limited number of studies that investigated neural changes after CBT in CFS [14] or CBT in other disorders (Seminowicz et al., [93]). However, those studies often relied on small samples (<20) and seldom used a no-treatment patient control condition. Here we overcome those problems by collecting data of more patients and by including a waiting list control condition. Because we will include twice as many patients in the CBT condition as in the waiting list condition, this study will allow us not only to investigate changes between CBT and waiting list conditions, but also to investigate changes within the CBT group between those patients that benefit from CBT and those that do not. This creates a unique change to investigate the neural mechanisms of change of CBT and to identify biomarkers that may predict treatment outcome.

We aim to replicated previously found anatomical findings [13, 14] and extend these findings with additional anatomical information using MRS and DTI. With respect to functional neuroimaging and behavioral assessment, task selection and hypotheses are based on a combination of clinical observations, cognitive behavioral models of CBT and a recent neurobiologically informed Bayesian model of medically unexplained symptoms. This translation between clinical observations and fundamental neuroscience models is unique in the investigation of CFS and an important step forward in understanding the etiology of CFS symptoms and the mechanisms of change of CBT.

Taken together, this project creates a unique opportunity to enhance our understanding of CFS symptoms and its change by CBT in terms of neuroanatomical, neurofunctional, behavioural, immunological and endocrinological mechanisms. Moreover, the comparison of patients that benefit from CBT with those that do not may lead to new insights for treatment resistant CFS patients.

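### The improved versus not-improved comparison within the CBT arm shows association with improvement, not a CBT mechanism, and splitting the patients in two costs power

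*Protocol article*

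**What the plan says.** The Analysis section of the protocol article plans three comparisons: patients against healthy controls at baseline; change in CBT against change on the waiting list; and change "between CFS patients within the CBT condition that show clinical significant improvement (see above) and those that do not". It also plans to relate neural measures to clinical measures, with no split stated, and to test by mediation analysis whether neural measures carry the effect of therapy on clinical outcome.

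Under Primary clinical outcome measures, success means "scoring lower than 35 and a reliable change index of >1.96 on the CIS subscale fatigue". Patients enter with a score of at least 40: "we will use cut-off score of ≥ 40 for inclusion of severely fatigued CFS patients".

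The Sample size section assumes that "approximately 50 % of the CFS patients in the CBT condition will show significant improvement" and gives this as the reason for including twice as many CBT patients as waiting-list patients. Study design gives the same reason for the 2:1 ratio. The Discussion says the design will serve to study how CBT brings about change and "to identify biomarkers that may predict treatment outcome". The Background states the principle for attribution: "The inclusion of a patient control condition is necessary to attribute changes seen in the treatment group to the intervention".

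**The concern.** The third comparison forms its groups from an outcome observed after randomisation, over the same interval as the neural change it is meant to explain, and in one arm only. If some neural measure moves whenever fatigue falls, for whatever reason, improved and not-improved CBT patients will differ on it. The comparison would look the same whether CBT acts through that measure or the measure merely follows how the patient feels. The Background's own argument for a patient control applies here, and this comparison has none.

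The comparison matters because it is the stated reason for the 2:1 allocation and it feeds the Discussion's expectations about mechanisms and predictors.

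The second issue is efficiency. Fatigue is measured on a scale from 8 to 56 but is reduced to two groups, in a study with only about 20 usable scans per group.

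**Working it through.** **1. The plan's own group sizes.** Inputs from the Sample size section: 60 CBT and 30 waiting-list patients, 17% dropout, 10% technical failure at each of two sessions, 50% success. The target comes from the statement that "the recommended number of subjects for between-group designs is 20".

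- CBT: 60 × 0.83 × 0.90 × 0.90 = 40.3
- Waiting list: 30 × 0.83 × 0.90 × 0.90 = 20.2
- Improved CBT patients: 40.3 × 0.50 = 20.2, and as many not improved

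The sizing reproduces. No stated figure is wrong.

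**2. How many successes could have occurred without CBT.** Input from the Sample size section: "mean decline of–15.2 (±15.8) for patients in the CBT condition and–5.2 (±7.2) for patients in the waiting list condition". Change is assumed normal. The mean baseline score and the reliability of the scale are not given, so the decline needed for success has to be assumed. The protocol's 50% success rate calibrates it: half of a normal distribution with mean 15.2 lies beyond 15.2, so the needed decline is about 15.2 points. The range 13 to 17 is an assumption around that value, and such a decline is taken also to meet the reliable-change criterion.

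The rate in each arm is 1 − Φ((needed decline − mean) / SD).

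| Needed decline | Waiting list | CBT | Ratio | Of 20 successes |
|---|---|---|---|---|
| 13 | 1 − Φ(1.08) = 0.139 | 1 − Φ(−0.14) = 0.555 | 0.25 | 5.0 |
| 15.2 | 1 − Φ(1.39) = 0.082 | 0.500 | 0.16 | 3.3 |
| 17 | 1 − Φ(1.64) = 0.051 | 1 − Φ(0.11) = 0.455 | 0.11 | 2.2 |

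Reading the ratio as the share of CBT successes that would have happened anyway also assumes that a patient who would improve on the waiting list would improve with CBT.

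**3. What the split costs.** With 40 patients and a linear relation between neural change and fatigue change, two-sided 0.05 tests were simulated: a correlation test on the continuous score, and a two-group t-test after a split at 50%. In theory such a split keeps 2/π = 0.64 of the information. The correlations are assumptions.

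| Assumed r | Continuous | Split | Loss |
|---|---|---|---|
| 0.30 | 0.48 | 0.33 | 0.15 |
| 0.40 | 0.74 | 0.54 | 0.20 |
| 0.43 | 0.81 | 0.60 | 0.21 |
| 0.50 | 0.92 | 0.75 | 0.17 |

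With 20 against 20, power of 80% needs a standardised difference of about 0.91.

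**4. Whether the waiting list could settle the matter through an interaction.** Simulated with 40 CBT and 20 waiting-list patients, the plan's change SDs of 15.8 and 7.2, and no association at all on the waiting list. Power for arm × fatigue change is about 0.09 at r = 0.3 in the CBT arm, 0.15 at r = 0.43 and 0.19 at r = 0.5. A real difference between the arms in slope would usually be missed.

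**The case against.** The strongest reply is that the plan does not depend on the third comparison for attribution. The second comparison is randomised, and a mediation analysis of therapy effects is by its nature an arm contrast. Both use the waiting list. This stands. A reader might infer from the third comparison that the trial as a whole sets its patient control aside, or reads spontaneous improvement as the action of CBT; the documents do not support that. The hypotheses on successful treatment are mostly phrased as changes that accompany it.

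Three further replies stand in part.

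- The planned analysis relating neural to clinical measures states no split and may already recover some of the lost information. The article does not say in which arms it is done or on what scale. In a condensed article that is no fault, but neither can it be counted as the repair.
- The split is not a bare cut-off, since a reliable change is also required. The figures in step 2 rest on an assumed needed decline because neither the baseline mean nor the reliability is given.
- The hope of finding predictors can be read as prognosis among treated patients, which one arm can address. A reader might take it as a claim about who benefits specifically from CBT. The text does not go that far, and the third comparison could not support it.

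None of this makes the within-arm contrast itself more than associational. The randomised comparison estimates the average effect of CBT and does not say what distinguishes success.

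**Conclusion.** The point holds for the third comparison, and only for it. As specified, it shows which neural changes go with improvement in treated patients and cannot tell a CBT mechanism from a correlate of any improvement. That limit would remain even if nobody improved spontaneously.

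Spontaneous improvement contaminates the contrast but does not explain it: about 3 of 20 successes, range 2 to 5, given normal change scores and a needed decline of 13 to 17 points. The conclusion that most of the contrast reflects natural recovery would be wrong on these figures.

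The loss from splitting is about 15 to 20 percentage points of power for assumed correlations of 0.3 to 0.5. It presumes a roughly linear relation and applies to the extent that the split is the main analysis. The correction is worth making because it is nearly free and because this comparison drove the allocation ratio.

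**What to change.** - Make the main analysis of the third comparison a regression of neural change on continuous change in the CIS fatigue score in the CBT arm, adjusted for baseline.
- Keep the improved/not-improved split as a descriptive display.
- Show the same slope for the waiting list with its confidence interval, as an imprecise exploratory check. Do not make an arm interaction a condition for any claim: step 4 shows that the test has too little power. It would also condition on a post-randomisation variable, so it would be no more causal than the split.
- Label the results of this comparison associational, and any predictors found in the CBT arm prognostic. Rest statements about mechanism on the randomised contrast and the mediation analysis.

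No new data and no change in sample size are needed, since the waiting list is already measured on the same schedule. The cost is slightly more analysis and softer claims from this comparison.
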